## Abstract

**Background:**

The global incidence of severe acute pancreatitis (SAP) is increasing, yet mortality rates remain persistently high. Novel therapeutic approaches are urgently needed to improve outcomes. The aim of this study is to evaluate the efficacy of high-dose intravenous vitamin C in improving organ support-free days within the first 14 days and other clinical outcomes in patients with SAP.

**Method:**

This is a prospective, randomized, double-blind, multicenter clinical trial. Participants will be stratified and randomly assigned to either the HDIVC group or the control group. Data will be analyzed using SAS 9.4 with two-sided tests and a significance threshold of *p* < 0.05. This study will be conduct at eight hospitals in China, including Shanghai Jiao Tong University School of Medicine Affiliated Ruijin Hospital, Shanghai General Hospital, Changhai Hospital, Sichuan Provincial People’s Hospital, Chongqing Daping Hospital, The Second People’s Hospital of Chengdu, Guanghan People’s Hospital and Chongqing Emergency Medical Center. Eligible patients are adults (age ≥ 18 years) diagnosed with severe acute pancreatitis according to 2012 Atlanta classification within 7 days of onset. HDIVC (500 mg/kg, 2 g/h) or placebo (normal saline) will be administered via central vein for 7 days. The primary outcome is organ support-free days within the first 14 days. Secondary outcomes include ICU all-cause mortality, changes in inflammatory biomarkers, and organ failure scores.

**Discussion:**

If proven effective, the results of this trial could establish high-dose intravenous vitamin C as a cost-effective adjunctive therapy to improve survival in patients with severe acute pancreatitis and potentially inform future clinical practice guidelines.

**Clinical trial registration:**

ClinicalTrials.gov, identifier NCT06897384.

## Introduction

Severe acute pancreatitis (SAP) is the most life-threatening form of acute pancreatitis (AP), and its incidence is rising globally (1). In Western countries, annual incidence runs from 13 to 45 per 100,000. In China, rates climbed from 0.19 to 0.71% over the past two decades. Mortality still sits between 13 and 35% despite better management (2).

Antioxidant therapy is important in SAP management. During early disease, oxidative stress from infection and uncontrolled reactive oxygen species (ROS) release triggers systemic inflammatory response syndrome (SIRS), which can progress to multiple organ dysfunction syndrome (MODS) (3). Therefore, timely elimination of excessive ROS is considered as a critical therapeutic target for improving clinical outcomes.

Vitamin C, a potent plasma antioxidant, effectively neutralizes ROS (3). Preclinical and clinical studies have demonstrated its anti-inflammatory properties and endothelial protective effects (4–6). Although oral administration is common (7), it fails to achieve therapeutic plasma concentrations in critically ill patients. Because critical illness drives rapid ROS overproduction and impairs gut absorption, oral dosing raises plasma levels to only around 150 μmol/L, well below what is needed to affect oxidative stress (8). Recently, high-dose intravenous vitamin C (HDIVC) has emerged as a promising intervention in critical care therapy. Growing evidence supports its potential efficacy in SAP, acute respiratory distress syndrome (ARDS), and severe coronavirus disease 2019 (COVID-19) (9).

HDIVC exerts multifaceted therapeutic effects through four pathways (10). Primarily, it functions as a potent antioxidant by directly eliminating ROS and reactive nitrogen species (RNS) while modulating enzymatic ROS through NADPH oxidase inhibition and other endogenous antioxidant system activation (11, 12). Second, as a critical cofactor in catecholamine biosynthesis, it bolsters hemodynamic stability through epinephrine and dopamine production. It simultaneously promotes vasopressin synthesis, raising blood pressure via R1 receptors, maintaining intravascular volume via R2 receptors, and increasing glucocorticoid synthesis via R3 receptor-driven ACTH release (13). Third, it contributes to immune defense by promoting lymphocyte proliferation, neutrophil chemotaxis and bacterial killing efficacy (13, 14). Finally, it decreases inflammatory activity through NF-kB pathway inhibition. These synergistic mechanisms position HDIVC as a promising therapeutic intervention for critical illness.

In our preclinical work, vitamin C supplementation lowered inflammatory markers, mortality, and pancreatic necrosis in SAP mice (15, 16). Whether this carries over to humans is unclear. Existing clinical data are inconsistent and come from small samples, insufficient dosing, or cohorts weighted toward mild disease (17). From September 2019 to December 2023, we conducted a single-center, double-blind, randomized, placebo-controlled trial (ChiCTR1900022022) investigating HDIVC (200 mg/kg/24 h, 1 g/h, for 7 days) (6). The primary outcome of 28-day mortality did not differ significantly between treatment groups in the overall cohort (*n* = 212). However, prespecified subgroup analysis revealed that MSAP patients receiving HDIVC demonstrated significant reductions in C-reactive protein levels and improved fluid balance. These findings suggest HDIVC may attenuate inflammatory responses in MSAP, though its therapeutic value in SAP requires confirmation through adequately powered multicenter randomized controlled trials. Extensive preclinical investigations over the past few decades have established the therapeutic potential of HDIVC in SAP, with mechanistic understanding progressively refined through cellular, animal, and early-phase human studies. While these foundational studies show biological plausibility, current clinical evidence remains limited to underpowered single-center trials, precluding definitive conclusions about therapeutic efficacy. To address this critical evidence gap, we propose a multicenter, prospective, randomized, double-blind, placebo-controlled trial evaluating early HDIVC administration (500 mg/kg/day for 7 days, 2 g/h) in SAP patients. The primary outcome is organ support-free days (OSFD) within the first 14 days. Secondary outcomes include ICU all-cause mortality, inflammatory biomarker, organ failure scores and fluid retention. This study aims to determine whether HDIVC represents a clinically meaningful, cost-effective therapeutic intervention capable of improving outcomes in this high-mortality condition, with potential to inform future guideline recommendations.

## Method and analysis

### Study design

This prospective, randomized, double-blind, multicenter trial will investigate whether early intravenous HDIVC reduces OSFD within the first 14 days in SAP patients. We will enroll 238 participants (119 per group) from eight hospitals across China, with block randomization allocating patients to either HDIVC or control groups. Serial assessments of organ function, disease severity scores, and mortality will be evaluated at predefined time points before and after treatment to determine therapeutic efficacy. The evaluation and examination will be continued from randomization to 180 days or death. Figure 1 shows the flow chart of the study. This study protocol is written according to the Standard Protocol Items for Randomization Trials (SPIRIT) statement (18).

**Figure 1 fig1:**
[figure not shown]
Flowchart of participants. This diagram shows the trial processes and outcome assessment. SAP, severe acute pancreatitis; ICU, intensive care unit; OSFD, organ support-free days; SOFA, sequential organ failure assessment; APACHE II, acute physiology and chronic health evaluation II; BISAP, bedside index for severity in acute pancreatitis; CTSI, CT severity index.

### Eligibility criteria

#### Inclusion criteria

Participants must meet the following criteria:

Age ≥ 18 years;Time from onset to enrollment is less than 7 days;Meets the diagnostic criteria for SAP per the 2012 Atlanta Guidelines, defined by persistent organ failure (modified Marshall score of 2 or higher lasting more than 48 h). Confirmation of the 48-h persistence must be completed within 7 days of disease onset.

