### Primary outcome

This study assesses the effect of HDIVC on organ support-free days (OSFD) within the first 14 days in SAP patients. OSFD refers to the number of days a patient does not require circulatory support (vasoactive agents), respiratory support (mechanical ventilation), or renal support (renal replacement therapy). For patients who die within the 14-day observation period, OSFD is assigned a value of 0 day.

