### Randomization and blinding

Participants will be strictly enrolled based on predefined eligibility criteria. Stratified block randomization will be employed by each research center. Patients will be allocated to either the HDIVC group or control group, with allocation concealment maintained throughout. Randomization numbers will be generated by statisticians using SAS 9.4 software, employing block randomization within each stratum to ensure balanced group assignment. Expansion of the sample size may be considered if necessary.

Stratification is performed at three levels: (1) participating center (8 centers), and (2) etiology, categorized as biliary, hypertriglyceridemic, alcoholic or other. Due to our rigorous inclusion criteria, all enrolled patients are diagnosed with SAP. We will not proceed stratification by disease severity. The randomization sequence is generated independently for each stratum combination (8 × 4 = 32 strata) by an independent statistician using SAS 9.4, employing variable block sizes of 4 and 6 (randomly alternated) to ensure allocation concealment and balance within each stratum.

To ensure blinding, study medications—either 50 mL vitamin C solution or matching placebo (0.9% normal saline)—will be prepared in identical, opaque, light-proof containers by UDPN according to the randomization list. Both groups will receive equal volumes (50 mL) via identical administration protocols using the standardized micropump (2 g/h). Crucially, the administration through a central vein minimizes potential sensory cues (such as infusion site irritation) that could arise from pH differences, thereby maintaining the blind for participants, clinical staff, and data analysts. All centers will follow this standardized protocol after thorough training and the study medicine is provided by one center to avoid bias.

The data management and analysis will implement a two-stage unblinding process. After all data have been locked following blinded data verification, the group assignments for each participant will be disclosed for statistical analysis. When the statistical analysis completes, the specific group assignments (intervention group or control group) will be disclosed to assess the study outcomes.

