Prespecified subgroup analyses will examine treatment effects by disease severity and baseline characteristics using interaction tests. All analyses will be performed using SAS 9.4, adhering to CONSORT guidelines.

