HDIVC represents a promising adjunctive therapy for SAP by targeting oxidative stress and systemic inflammation. If proven effective, the study may provide evidence to support future guidelines. However, several challenges still remain. Patient heterogeneity and variability in disease course may influence treatment response. Patients >100 kg are excluded because weight-based dosing in predominantly adipose excess could yield a disproportionately high drug load. The 50 g/d cap is consistent with established safety limits (21), though this limits generalizability to obese SAP patients. Inter-center variability in supportive care is inevitable in a pragmatic eight-center trial. We mitigate this through centralized training, protocol-driven management, including center as a random intercept, and prospectively recording concomitant therapies. Timely enrollment is critical to capture the early inflammatory phase, but in clinical practice, delays in diagnosis or transfer may limit early intervention. To avoid this as far as possible, we set a 7-day cutoff from the onset of the disease during which vitamin C may exert therapeutic effect on SAP. But the 7-day enrollment window requires organ failure documentation by Day 5 to meet the Atlanta SAP criteria, which may delay or preclude enrollment.

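### Entry does not require organ failure or support at randomisation, so some patients may have less room to gain OSFD, and the severity subgroup has one level on the trial's own classification

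*Protocol article*

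**What the plan says.** **Entry.** The Inclusion criteria ask for SAP "defined by persistent organ failure (modified Marshall score of 2 or higher lasting more than 48 h). Confirmation of the 48-h persistence must be completed" by day 7 after onset. Enrolment has its own limit: "Time from onset to enrollment is less than 7 days". Both limits are counted from onset. The Exclusion criteria contain nothing on organ failure that has resolved. The Discussion comments that "the 7-day enrollment window requires organ failure documentation by Day 5 to meet the Atlanta SAP criteria", which again concerns when failure was documented, not whether it is still present.

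**Outcome.** Under Primary outcome, "OSFD refers to the number of days a patient does not require circulatory support (vasoactive agents), respiratory support (mechanical ventilation), or renal support". Death within the 14 days scores 0.

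**Severity.** Randomization and blinding stratifies by center and etiology and explains why severity is left out: "all enrolled patients are diagnosed with SAP. We will not proceed stratification by disease severity". The last paragraph of Statistical methods nevertheless says: "Prespecified subgroup analyses will examine treatment effects by disease severity and baseline characteristics using interaction tests". It gives no levels for severity and does not name the baseline characteristics.

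**Baseline support.** Table 1 records renal replacement, mechanical ventilation and vasoactive drugs at Day 0. The primary model, as described in Statistical methods, names center only. The Intervention section promises that CRRT parameters will enter adjustments and subgroup analyses, for the purpose of studying drug exposure.

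**The concern.** Entry is set by an organ-failure score over a past spell; the outcome counts three specific supports from here on. The two need not coincide. Take a patient with organ failure from Day 1 to Day 4 that resolves on Day 5, enrolled on Day 6: every criterion is met. So it is for a patient whose score stays at 2 or more without any of the three supports. Both begin the trial support-free.

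The aim is to show added support-free days. A patient who is on support can gain by coming off it sooner. A patient who is not can gain only by avoiding later support or death. If many patients are of the second kind, the average difference may be smaller than the 2 days planned for. A null result would then be hard to read: no effect, or a population with little support left to shorten. The analysis that would help most is the treatment effect by support status at entry. The document names severity instead, and on its own classification severity does not vary.

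**Working it through.** **1. The plan's own figure.** Inputs from Sample size: difference 2 days, SD 5, two-sided α 0.05, power 0.80, 15% inflation for non-normality, 5% dropout.

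- n per group = 2 × [5 × (1.960 + 0.842) / 2]² = 98.1, stated as 98.
- 98 × 1.15 = 112.7, so 113.
- 113 / 0.95 = 118.9, so 119 per group and 238 in total.

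The stated 238 reproduces. The sample-size arithmetic is not at fault.

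**2. Reference power.** The 15% is there to pay for non-normality, so it should not be counted as extra power. Effective n = 113 / 1.15 = 98.3 per group; SE = 5 × √(2 / 98.3) = 0.713; power = Φ(2 / 0.713 − 1.96) = 80%.

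**3. Worst case.** Let f be the share who start support-free. The documents do not give it; 10% to 30% is an assumption. Suppose these patients gain nothing, the rest gain 2 days, SD stays at 5, and the 14 days run from randomisation. Then the mean difference is 2(1 − f) and power = Φ(2(1 − f) / 0.713 − 1.96).

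| f | Mean difference (days) | Power | Gain needed in the rest for a 2-day average, 2/(1 − f) | Total N for 80% by the plan's steps |
|---|---|---|---|---|
| 0 | 2.0 | 80% | 2.0 | 238 |
| 10% | 1.8 | 71% | 2.2 | 296 |
| 20% | 1.6 | 61% | 2.5 | 372 |
| 30% | 1.4 | 50% | 2.9 | 486 |

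**4. Sensitivity to the two main assumptions.**

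- *Some benefit in support-free patients.* If they gain 1 day instead of none, the mean difference is 2(1 − f) + f = 2 − f, that is 1.9, 1.8 or 1.7 days. Power is Φ(1.9/0.713 − 1.96) = 76%, then 71% and 66%.
- *A wider SD.* If support-free patients all score 14 and the rest have mean 5 to 7 days and SD 5 (both assumed), the variance is (1 − f) × 25 + f(1 − f)(14 − m)², where m is the mean of the rest. The SD is then 5.2 to 5.9, and power is about 64–68%, 50–57% and 39–46% at f = 10%, 20% and 30%.

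**5. The severity passages side by side.** Randomization and blinding declines to stratify by severity because everyone enrolled has SAP. Statistical methods then examines the treatment effect by disease severity with an interaction test. If severity means the Atlanta class, as it does in the first section, the factor has one level and there is no interaction to test. If it means something else, the document does not say so there. Secondary outcome uses disease severity scores for APACHE II and BISAP, so another meaning is possible.

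**The case against.** A reader might infer that support-free patients are already at the ceiling of OSFD and cannot show a benefit. The documents do not support that. OSFD is counted over 14 days, so new ventilation, vasoactive treatment or renal replacement lowers it, and death sets it to 0. The trial compares arms, so preventing that loss counts as a gain, and Expected results names halting the progression of organ dysfunction as the mechanism. Zero gain is therefore only the worst case. What remains is less room for benefit.

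A reader might also infer that the planned subgroups cannot separate these patients. That too goes beyond the text. APACHE II or BISAP would separate them imperfectly, the unnamed baseline characteristics could include organ support, CRRT subgroups are promised, and all three supports are recorded at Day 0. Levels and factor lists are often left to an analysis plan, which is not shown here, so their absence is not the point. The point is that two sections treat severity in ways that do not fit together. The CRRT subgroups concern drug exposure and cover one support of three.

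On size, the objection is strong. No share is given, and nothing shows that late enrolment after resolved failure would be common. The 2 days in Sample size are stated for the HDIVC group as a whole; if that average already allows for support-free patients, there is no shortfall. The power figures follow from placing the 2 days in supported patients only.

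Finally, entry by the Atlanta definition is a legitimate choice for a question about SAP. Requiring a qualifying score shortly before randomisation would narrow the population after 34 patients have been recruited, and would still admit those who have the score but no support.

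**Conclusion.** The point holds in limited form. The criteria do not require organ failure or organ support at randomisation, so some patients may enter with less room to gain on the primary outcome. In the worst case, power falls from 80% to about 71%, 61% or 50% for shares of 10%, 20% or 30%. This rests on assumed shares, no gain in support-free patients, a 2-day gain in the rest, and SD 5. It is a range, not an estimate, and partial benefit would make the loss smaller.

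The firmer part is textual. On the classification in Randomization and blinding, the severity subgroup in Statistical methods has a single level, and baseline organ support, the factor most directly tied to OSFD, is not named for the primary analysis. It is worth correcting because the correction is cheap. It does not invalidate the design or the sample-size calculation.

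**What to change.** Reconcile Randomization and blinding with Statistical methods. In the prespecified subgroups, replace disease severity by the number of organ supports at Day 0 (0, 1, 2 or more), counting vasoactive agents, mechanical ventilation and renal replacement. Report the treatment effect on OSFD within each level, with the interaction test. Preferably, also enter the same variable as a baseline covariate in the primary mixed model. State that the Day 0 status is the one before the first infusion.

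**Cost.** One or two lines of wording and no new data, since Table 1 already records the three supports at Day 0. It should be settled before the interim analysis so that it is plainly prespecified. The downside is low power for the interaction in a trial of 238, so the subgroup should be read as supportive and not as a second route to a positive claim.

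Whether to require ongoing organ failure at entry is an eligibility trade-off for the sponsor to decide; this fix does not depend on it.

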#### Exclusion criteria

Participants who meet any of the following criteria will be excluded from the study:

SAP caused by tumors or ERCP;Pregnancy or breastfeeding;Allergy to vitamin C;Use of other experimental drugs during the study period;Pre-existing chronic organ failure affecting the heart, liver, lung, or kidney prior to admission, defined as: chronic cardiovascular dysfunction requiring long-term mechanical hemodynamic support or inotropic drugs; chronic obstructive pulmonary disease requiring home oxygen therapy; chronic liver failure classified as Child-Pugh grade C; chronic kidney disease defined by eGFR less than 60 mL/min/1.73 m^2^ (CKD-EPI 2021). Baseline creatinine is based on stable outpatient values from the past 6 months; if unavailable, exclusion relies on a documented history of chronic kidney disease rather than an acute admission creatinine.Immunosuppressive states, including malignant tumors, post-transplant conditions, long-term use of immunosuppressor (for at least 1 month before enrollment), or AIDS;Refuse to sign the informed consent form;Weight > 100 kg;Presence of urinary tract stones identified during the current admission (including symptomatic clinical events or incidental findings on baseline abdominal imaging).Known personal or strong family medical history of G6PD deficiency (routine laboratory screening is not required prior to enrollment).

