To ensure pharmacological consistency across centers, the study medication is standardized. Vitamin C is sourced from a single manufacturer (Chengdu Brilliant Pharmaceutical Co., Ltd., Chengdu, China; National Medicine Permission Number: H32022732) from one production batch. The medication is supplied in ampoules of 1 g per 5 mL (200 mg/mL). The solvent is water for injection, with sodium metabisulfite, cysteine hydrochloride, disodium edetate, and anhydrous sodium carbonate as excipients. To avoid fluid overload in SAP patients, vitamin C is given as the undiluted original solution. For the intervention group, the weight-based dose (500 mg/kg/day) is drawn into 50 mL light-proof syringes by an unblinded drug preparation nurse (UDPN). The solution is administered continuously via a central venous catheter using a micro-infusion pump at 2 g/h. The control group receives 0.9% normal saline at 10 mL/h to match the vitamin C infusion, for a daily sodium chloride load of approximately 2.16 g. Throughout the intervention period, patients will be closely monitored for adverse effects. If complications such as cystinuria, gout, hyperoxaluria, oxalate deposition, or urate kidney stones occur, the dosage should be adjusted as clinically indicated. In severe cases, the trial may be discontinued.

During the intervention, if an interruption occurs (such as CT transport, infusion pump disconnection, central line failure) the infusion will be temporarily paused and later resumed at the identical constant rate of 2 g/h. Catch-up boluses or rate increases are prohibited. Interruptions under 2 h per 24-h cycle are considered acceptable. Longer interruptions are documented as protocol deviations but the patient remains in the study under ITT analysis.

Vitamin C has low molecular weight and high water solubility, so it is cleared during CRRT. The baseline dose is high enough that plasma levels should stay well above the therapeutic threshold even during continuous renal replacement therapy (CRRT). Keeping the dose unchanged avoids rebound toxicity risk if CRRT is interrupted unexpectedly, and it keeps the protocol consistent across all study centers. We will document CRRT parameters (duration, modality, effluent dose) in Table 1 and include them in statistical adjustments and subgroup analyses to capture how CRRT affects drug exposure.

**Table 1 tab1:** Collected procedures, data, and outcomes.

Procedures	Day 0	Day 1	Day 3	Day 7	Day 14	Day 28	Day 180

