During the treatment period, if complications such as urinary crystals or unexplained acute kidney injury (meeting KDIGO guidelines) occur, emergency unblinding will be performed in accordance with GCP procedures. The attending physician will immediately notify both the site principal investigator and the study-wide principal investigator, who will jointly evaluate the event and determine appropriate clinical management. All such events will be documented and reported to the institutional review board as required.

To reduce the risk of unblinding from pronounced clinical responses, several strategies have been implemented. First, the initiation, titration, and withdrawal of life-sustaining therapies (vasopressors, mechanical ventilation, and CRRT) are protocol-driven. Bedside clinicians follow objective physiological targets and international guidelines rather than subjective judgment. Second, the primary outcome (OSFD within the first 14 days) is a definitive, objective outcome not subject to observer bias. Third, clinical data extraction and calculation of secondary outcomes (SOFA and modified Marshall scores) are performed by independent, blinded research personnel not involved in daily patient management. Investigators will monitor and record events that could lead to unblinding, including unexplained severe AKI or suspected oxalate nephropathy, and spurious glucose readings or glucometer errors.

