#### Treatment discontinuation criteria

Study drug infusion must be discontinued immediately for any of the following events. Emergency unblinding may be performed if deemed necessary by the attending physician:

(1) new-onset AKI meeting KDIGO Stage 2 or 3 (serum creatinine ≥ 2.0 × baseline or urine output < 0.5 mL/kg/h for ≥ 12 h) judged as potentially related to vitamin C-associated oxalate nephropathy.(2) microscopic urinalysis showing abundant calcium oxalate crystals (≥50 per high-power field) with acute creatinine rise.(3) clinical or laboratory evidence of hemolytic anemia (sudden hemoglobin drop, elevated indirect bilirubin, hemoglobinuria).(4) confirmed hypoglycemia (<3.9 mmol/L) after excluding glucometer interference by venous blood gas confirmation.(5) any SAE judged as possibly or definitely related to the study drug.

Both AEs and SAEs will be evaluated at 8:00 a.m. every day. Investigators are required to promptly assess the aforementioned adverse events. If the investigator determines that an abnormal laboratory result is clinically significant and not part of the clinical condition, it should be recorded as an adverse event and report to the PI of each research site. Once confirmed, the intervention should be discontinued immediately and proper medication should be taken.

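### Known hyperoxaluria, cystinuria and gout are not addressed at entry, although the protocol lists them as complications that change dosing, and conditions already present are not separated from new ones

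*Protocol article*

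**What the plan says.** All places are in the protocol article.

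- **Exclusion criteria, stones:** "Presence of urinary tract stones identified during the current admission (including symptomatic clinical events or incidental findings on baseline abdominal imaging"). The criterion is tied to the present admission.
- **Exclusion criteria, kidney:** "chronic kidney disease defined by eGFR less than 60 mL/min/1.73 m^2^ (CKD-EPI 2021").
- **Exclusion criteria, G6PD:** "Known personal or strong family medical history of G6PD deficiency (routine laboratory screening is not required prior to enrollment"). This criterion rests on history.
- **Intervention:** "Throughout the intervention period, patients will be closely monitored for adverse effects". The next sentence reads: "If complications such as cystinuria, gout, hyperoxaluria, oxalate deposition, or urate kidney stones occur, the dosage should be adjusted as clinically indicated". The section also allows for stopping the trial when such a complication is severe.
- **Randomization and blinding:** "if complications such as urinary crystals or unexplained acute kidney injury (meeting KDIGO guidelines) occur, emergency unblinding will be performed".
- **AEs include:** the presence of urinary crystals is the first listed event, with no count threshold and no requirement that it be new.
- **Treatment discontinuation criteria:** one criterion is "microscopic urinalysis showing abundant calcium oxalate crystals (≥50 per high-power field) with acute creatinine rise"; another requires new-onset kidney injury. The closing paragraph limits the recording of laboratory abnormalities to those that the investigator considers clinically significant and not explained by the underlying illness.
- **Table 1:** medical data are collected at Day 0. The laboratory footnote lists blood tests and no urinalysis. The safety section places urine testing in the treatment period.

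**The concern.** The protocol identifies certain metabolic and stone-related conditions as consequences of the study drug that matter enough to alter treatment. A patient may arrive with one of them already on record. If no stone is seen in this admission and no other exclusion applies, that patient is eligible as the text stands, and the protocol does not say how the listed condition is then to be read.

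Two things are at stake. The first is safety: patients whom the protocol's own list marks as at risk can be assigned seven days of high-dose infusion without the plan having considered them. The second is attribution: secondary outcome (9) counts adverse events related to vitamin C, and crystals that reflect a condition present before randomisation can enter that count or lead to a broken code, in either arm.

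**Working it through.** The point rests mainly on setting the sections side by side.

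**Step 1. Match the list of complications against the exclusions.**
- Urate kidney stones: partly covered, by the current-admission stone criterion.
- Oxalate deposition: no criterion names it. The kidney criterion removes only patients who also have chronic kidney disease.
- Hyperoxaluria, cystinuria and gout: no criterion names them. A patient with one of these, no stone on this admission and no chronic kidney disease passes the list.
- G6PD deficiency: covered, by known personal or strong family history.

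So the sponsor already accepts a history-based check without a laboratory test for one vitamin C hazard, but has not used it for conditions that its own Intervention section names.

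**Step 2. Read the dosing sentence for timing.** It follows a sentence about monitoring during the intervention period and speaks of complications that occur. A new event is plainly covered. For a condition already present at baseline the text gives no instruction: it neither includes nor excludes it.

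**Step 3. Follow urinary crystals through the safety sections.**
- The unblinding paragraph and the adverse event list have no threshold and no new-onset qualifier.
- The discontinuation criterion does have both a count and an acute creatinine rise.
- No urinalysis is listed at Day 0, so the article states no baseline against which a later finding is judged.

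Crystals arising from a standing condition can therefore count under the first two sections without meeting the third.

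**Step 4. Size.** The plan states no figure on this point. The only trial figure used is the sample size, which reproduces: 2 × (1.96 + 0.8416)² × 5² / 2² = 98.1 per group (stated as 98; 99 if rounded up); 98 × 1.15 = 112.7, so 113; 113 / 0.95 = 118.9, so 119 per group and 238 in total. The point does not change it.

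With no prevalence in the documents, only a scaling is possible: 0.01 × 238 = 2.4 patients and 0.01 × 119 = 1.2 per arm for each percentage point of participants with such a history. This is not an estimate of the percentage.

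**Step 5. Exposure.** At 100 kg, the highest weight allowed, the stated dose is 0.5 g/kg × 100 kg × 7 days = 350 g. The stated rate delivers at most 2 g/h × 24 h × 7 days = 336 g, so 336 g is the ceiling if the rate is followed. At 50 kg the dose is 0.5 × 50 × 7 = 175 g.

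**The case against.** **A list of complications is not a list of exclusions.** Acute kidney injury is a listed adverse event, yet renal failure is one route into the trial. This stands: the sections do not contradict each other outright, and whether gout, for instance, should bar entry is the sponsor's judgement. What remains is that the plan is silent on known cases.

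**Stones and G6PD deficiency are detected differently.** A Day 0 abdominal CT can show a silent stone, whereas G6PD deficiency cannot be imaged and laboratory screening is waived. This explains why the stone criterion relies on imaging. It does not explain the silence on metabolic conditions that imaging cannot show and history could.

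**Old and new events can be separated already.** Day 0 medical data are collected, the investigator screens out laboratory findings that belong to the illness, and the discontinuation criteria require new-onset injury or an acute creatinine rise. This stands in part. The investigator's filter does not mention pre-existing metabolic conditions, and it does not qualify the unblinding trigger.

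**Randomisation spreads such patients over both arms.** This stands: the effect is mainly noise in one safety outcome and some avoidable code breaks, not systematic bias.

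A reader might also infer that such patients meet the dose-adjustment trigger before the first dose. The text does not support that, because it concerns complications that occur under monitoring during treatment. Nor are past, resolved stones on the list: it names urate stones that occur, and a patient with only an old stone meets no trigger in the document.

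**Conclusion.** The point holds as a gap between sections. Entry criteria do not address known hyperoxaluria, cystinuria or gout, the dosing paragraph leaves baseline conditions undefined, and urinary crystals count as an event and an unblinding trigger without having to be new. The article prints its exclusions in fine detail and limits the stone criterion explicitly to the current admission, so this is not detail left to a fuller document.

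The consequence is modest. It concerns the safety of a probably small number of patients, the reading of secondary outcome (9), and the blind for individual patients. The primary outcome, its analysis and the sample size are unaffected.

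The number of patients cannot be computed. A reader might assume a prevalence of a few per cent and conclude that pre-existing cases could equal the treatment-emergent ones. The documents give neither a prevalence nor an event rate, so that comparison has no support. The conclusion rests on one assumption: that some otherwise eligible patients arrive with a listed condition already documented.

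**What to change.** Reconcile the exclusion criteria, the Intervention section, the unblinding paragraph and the adverse event list.

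1. Address at entry, by known history and with no new test, the conditions that the Intervention section lists. The sponsor decides which of them exclude a patient. Past, resolved stones may be added but need not be, since the list does not name them.
2. Say in the Intervention section whether a listed condition present at baseline counts.
3. For any condition kept eligible, record it at Day 0 and count only new or worsened events in secondary outcome (9).
4. State whether urinary crystals must be new or worsened to count as an adverse event and to trigger unblinding, and align that wording with the discontinuation criteria.

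The cost is one line in the exclusion list, one history item within the medical data already collected at Day 0, and short wording changes in the safety sections. A few patients may become ineligible; how many cannot be derived from the documents.
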